### **Masking**

In a study of this type it is impossible to mask the intervention. The analysis data will be performed by independent professionals blinded to the assignment group.

Intervention:

a. In the control group:

Routine clinical practice: The clinical approach of the patients will be done following the recommendations of clinical practice guidelines as detailed in Table 
2.

b. In the intervention group:

Besides the routine clinical practice, four weekly cognitive-behavioral group sessions of 2 hours guided by nurse professionals will be carried out in the PHCC. The groups will be made up by 6–12 patients.

The content of the sessions will be as follows (Table 
3):

**Table 3 T3:** Structure of the group sessions in the intervention group

1.	COGNITIVE REATTRIBUTION
	· Psychological explanation of the symptoms: To explain the objective of the session that is not precisely to heal the symptoms, but rather “to improve doping". To explain that somatization is a common phenomenon resulting from different factors and mechanisms. The patients are asked to talk about the different factors; and stress is introduced as an explanatory element of the symptoms.
	· The importance of the cognitive issue. They give examples on the role of knowledge and the patients are asked to link them to their own experiences. The objective is to show how the behaviors and the attitude toward the symptoms could change the response to them.
2.	RELAXATION AND SYMPTOMATIC RELIEF
	· Once the role of stress in the genesis of pain has been described, techniques are introduced where physical exercising and muscular relaxation are combined. The patients are provided with a CD with spoken instructions.
3.	BEHAVIOR-ILLNESS
	· The patients are given details on optional treatments and on the correct use of sanitary services. They are also instructed on the mechanisms to control anomalous behavior toward the illness.
4.	AEROBIC EXERCISING
	· To encourage physical exercising: to do away with the bad habit of stating that “pain stops me from doing any kind activity” thus, they avoid doing any kind of activity. An ongoing program on physical exercising is outlined.

If the study results prove that the intervention is effective, cognitive behavioral sessions are planned for the patients in the control group.

Before starting the intervention itself, will develop the training for professionals involved in the study. In order to make the best use of the diagnosis and the therapeutic approach on the patients that have been identified as suffering from anxiety and/or depression disorders, and to standardize clinical practice, a two-hour initial training session will be carried out for all the doctors that participate in the study. The session will have the following content: train in the use of the PRIME-MD questionnaire; as well as in upgrading the rules on pharmacological treatment of the detected pathologies. In addition will be reviewed Standards for GCP for approaching the patients with MUS (Table 
2).

Besides, there will be a ten-hour specialized training session aimed to the nurses in charge of perform the intervention at each center, reattribution techniques and cognitive-behavioral, that underlie the intervention group.

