### **Data collection method**

The doctor will recruit the patients and will assess the selection criteria. He will let the patient know about the objectives of the study; and will request his informed consent.

All patients who accepted to participate will get the SF-12 questionnaire on quality of life at the end of the doctor’s examination. Furthermore, all patients will get the PRIME-MD questionnaire to identify any psychiatric co-morbidity that will be treated by the doctor according to his criterion.

At 3, 6 and 12 months (visits V2, V3 and V4, respectively) will be referred the patient to evaluate the usefulness of cognitive-behavioral sessions, and completion of quality of life questionnaire (SF-12) and Clinical Global Impression of patient and physician (PGI and CGI).

The structure of the study is described in Table 
4.

**Table 4 T4:** Project structure

	**Intervention Group**	**Control Group**
**Recruitment visit (V 0)**	Selection criteria	
Consecutive selection	Request on informed consent	
	PRIME MD Questionnaire	
	Variables:	
	· SF-12 Questionnaire on life quality	
	· Descriptive variables: sex, cultural level, age, months with symptoms, time on antidepressants consumption, requested tests y specialized derivations to	
**Training of professionals involved**	Training in management of PRIME-MD survey. Review of Standards of Good Clinical Practice	
	Training in cognitive-behavioral (Only intervention Group)	
**Baseline visit (V1)**	Variables:	
	· SF-12 Questionnaire	
	· Prescribed medicine	
	· Requested tests	
	· Derivations to secondary level	
	· Days of sickness absence	
	· Assessment of compliance with the standards of good clinical practice	
	· Questionnaire on global clinical impression; both, the doctor and the patient	
**Intervention**	There will be a weekly group session for 4 weeks (Only intervention Group)	
	Routine clinical practice	
**3-months post Intervention visit (V2)**	Variables:	
	· SF-12 Questionnaire	
	· Prescribed medicine	
	· Requested tests	
	· Derivations to secondary level	
	· Days of sickness absence	
	· Assessment of compliance with the standards of good clinical practice	
	· Questionnaire on global clinical impression; both, the doctor and the patient	
	· Assessment by the nurse subject participation.	
	· Assessment of cognitive- behavioral module by subject (Only intervention Group)	
**6-months post Intervention visit (V3) 12-months post Intervention visit (V4)**	Variables:	
	· SF-12 Questionnaire	

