#### ***Clinical Variables***

– Duration of the somatic symptoms before the study. Quantitative variable (number of months).

– Time on anti-depressants consumption (months) before the study.

– Psychiatric Co-morbidity at the beginning of the study. It will be analyzed as a dichotomy qualitative variable (yes/no); assessing the presence/absence of depression, anxiety and somatic-morph disorders (according to the PRIME MD classification).

– PRIME-MD questionnaire; validated in Spain 
[27] that categorizes the patient into 5 areas of mental disorders with greater incidence on primary care: disorders in the state of mind/mood, anxiety disorders, disorders on nutritional behavior, somatoform disorders and disorders due to alcohol abuse or addiction. There are two components: a questionnaire for the patient that acts as a sifting/testing tool, and an assessment guide for the doctor that allows the diagnostic confirmation on the case. Once the questionnaire has been carried out, the patients diagnosed under anxiety or depression will be treated in a standardized way. Thus a bias is eliminated in the understanding of the study results, i.e. not to have treated the identified anxious-depressive psychiatric co-morbidity in a proper way; an issue that could have positive effect on the somatoform manifestations.

– Derivations carried out at secondary level.

– Complementary Tests, grouped in the following categories: laboratory, image tests, and endoscopies.

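### Table 4 gives PRIME-MD only at the recruitment visit and trains doctors in it afterwards, which weakens the baseline co-morbidity variable and the standardisation it should support

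*Protocol article*

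**What the plan says.** The training plan sits under Masking. Its timing is given in one clause: "Before starting the intervention itself, will develop the training for professionals involved in the study". For doctors in both arms, "a two-hour initial training session will be carried out for all the doctors that participate in the study". Its content is to "train in the use of the PRIME-MD questionnaire; as well as in upgrading the rules on pharmacological treatment of the detected pathologies", together with a review of the good-practice standards in Table 2. The stated purpose concerns "the patients that have been identified as suffering from anxiety and/or depression disorders".

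Under Data collection method, "The doctor will recruit the patients and will assess the selection criteria", and every patient who agrees to take part receives the "PRIME-MD questionnaire". Table 4 lists that instrument in the V0 block. The next row, before the V1 block, is the training of professionals: "Training in management of PRIME-MD survey. Review of Standards of Good Clinical Practice". The nurses' cognitive-behavioural training is in the same row.

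Clinical Variables describes PRIME-MD as having two parts: a screening form for the patient and "an assessment guide for the doctor that allows the diagnostic confirmation on the case". The result becomes a yes/no variable for psychiatric co-morbidity at the start of the study. It also identifies patients whose anxiety or depression is to be treated in a standardised way, and the section concludes that a source of bias has thereby been removed.

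**The concern.** The protocol itself treats doctor training as necessary for using PRIME-MD well and for standardising practice. If training comes after the instrument's only scheduled use, it cannot serve that purpose. Three things rest on the V0 result: the description of co-morbidity at baseline, any adjustment for it, and the detection of patients for standardised treatment. If doctors at 14 centres use the instrument without common instruction, the yes/no variable may partly reflect differences between doctors or centres rather than between patients. The claim that inadequately treated co-morbidity no longer clouds the results would then lack its stated support.

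**Working it through.** The plan gives no figure on this point to reproduce. The check is one of sequence.

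1. **Is Table 4 in time order?** Its blocks run V0, training, V1, intervention, V2, then V3 and V4. The visit labels ascend, and the intervention sits between baseline and the three-month visit. Two further features fit training placed between V0 and V1: the SF-12 is taken at both visits, and compliance with the good-practice standards is first recorded at V1, after the row in which those standards are reviewed.

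2. **Where does PRIME-MD appear?** It is in the V0 block and in none of the blocks for V1, V2, V3 or V4. That is 1 of 5 visits, and 0 of the 4 visits after the training row. The text on the 3, 6 and 12 month visits names the SF-12, the two global impression scales and the usefulness of the sessions, and not PRIME-MD. The global impression scales are not diagnostic, so they do not replace it.

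3. **Does the text put training earlier?** The only anchor under Masking is the start of the intervention. Training between V0 and V1 satisfies it, and so would training before V0. The text therefore does not contradict the table and does not protect recruitment. The description of patients as already identified fits the table's order.

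4. **Does the order matter for this instrument?** Diagnostic confirmation depends on the doctor working through the guide. If that is done at V0, an untrained doctor does it, and no later visit is scheduled to correct it. Up to all 242 planned patients are affected; fewer if the guide is completed later than V0.

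5. **Which analyses are touched?** The chi-squared comparison in Statistical Analysis does not use the co-morbidity variable. The random-effects logistic model adjusts for prognostic factors that are not named. Co-morbidity is a candidate, so adjustment suffers only if it is included.

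6. **A related conflict.** Data collection method leaves treatment of detected co-morbidity to the doctor's own judgement. Clinical Variables says it is standardised. The session that is meant to bring standardisation comes after V0 in Table 4, so the two statements cannot both be read as applying from recruitment onward.

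**The case against.** The strongest reply is that no sentence says training follows recruitment. The clause under Masking is equally true of training held before V0, the session is called initial, and Table 4 mixes patient visits with a staff activity. This stands as a limit on certainty: the point rests on row order. It does not remove the point, because the table is the only place where the two events are ordered, and the word initial is attached to no visit. Nor is this detail left to a fuller document, since the article states a sequence.

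A second reply is that the doctor's guide is not dated separately from the patient's form, so screening at V0 with confirmation after training is possible. This also stands. It would rescue the diagnosis, but the protocol schedules no such later step.

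Some stronger readings are tempting but unsupported:

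- **Eligibility.** A reader might infer that eligibility is compromised because PRIME-MD covers alcohol problems and addiction is an exclusion. Nothing links the instrument to that criterion, and PRIME-MD is given to patients who have already agreed to take part.
- **Bias in the primary result.** Doctors in both arms receive the same session, so the documents give no reason to expect errors that differ by arm. With 14 centres allocated by simple randomisation, chance imbalance in co-morbidity is possible, but the documents do not show that it would be material.
- **Misplaced patients.** Anxiety or depression as such is not an exclusion, so these patients could enter the groups whether or not they are recognised.
- **A figure for misclassification.** The documents give no sensitivity or specificity, trained or untrained, so the loss from the order of events cannot be quantified.

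**Conclusion.** The point holds in a limited form. As scheduled, the instrument is used before the training that is meant to make its use reliable and uniform. The affected items are secondary: baseline description, adjustment if co-morbidity enters the model, and the standardisation claim in Clinical Variables. It should be corrected because the remedy is cheap, but it does not threaten the validity of the primary comparison. The conclusion assumes that Table 4 is chronological and that confirmation with the guide takes place at V0 along with the patient's form. If the second assumption fails, what remains is the need to state when confirmation occurs and by whom.

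**What to change.** Hold the PRIME-MD part of the doctors' session before the first V0 at each centre. It is common to both arms, so moving it discloses no allocation. Leave the Table 2 review and the nurses' training between V0 and V1. Moving the review as well would lose the SF-12 measurement that now precedes it, and the article states an aim of assessing the good-practice rules. Amend Table 4 and the training paragraph under Masking to match, and say when the doctor's guide is completed.

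Alternatively, or for patients already recruited, have the trained doctor complete the guide at V1 before the sessions start, and take the co-morbidity variable from that. This is the weaker option: V1 follows any treatment begun after V0, and it follows nurse training given only in intervention centres, so the doctor may know the arm.

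Reconcile Data collection method, Clinical Variables and the training paragraph on whether detected co-morbidity is managed at the doctor's discretion or in a standardised way. Which it should be is for the investigators to decide.

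The cost is one split or rescheduled two-hour session, or about ten minutes per patient at an existing visit, using the application time given in the Discussion. No new staff, visit or instrument is needed. If training was always meant to come first, reordering Table 4 and adding a clause to the training paragraph is enough for the timing.

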### **Data collection method**

The doctor will recruit the patients and will assess the selection criteria. He will let the patient know about the objectives of the study; and will request his informed consent.

All patients who accepted to participate will get the SF-12 questionnaire on quality of life at the end of the doctor’s examination. Furthermore, all patients will get the PRIME-MD questionnaire to identify any psychiatric co-morbidity that will be treated by the doctor according to his criterion.

At 3, 6 and 12 months (visits V2, V3 and V4, respectively) will be referred the patient to evaluate the usefulness of cognitive-behavioral sessions, and completion of quality of life questionnaire (SF-12) and Clinical Global Impression of patient and physician (PGI and CGI).

The structure of the study is described in Table 
4.

**Table 4 T4:** Project structure

	**Intervention Group**	**Control Group**
**Recruitment visit (V 0)**	Selection criteria	
Consecutive selection	Request on informed consent	
	PRIME MD Questionnaire	
	Variables:	
	· SF-12 Questionnaire on life quality	
	· Descriptive variables: sex, cultural level, age, months with symptoms, time on antidepressants consumption, requested tests y specialized derivations to	
**Training of professionals involved**	Training in management of PRIME-MD survey. Review of Standards of Good Clinical Practice	
	Training in cognitive-behavioral (Only intervention Group)	
**Baseline visit (V1)**	Variables:	
	· SF-12 Questionnaire	
	· Prescribed medicine	
	· Requested tests	
	· Derivations to secondary level	
	· Days of sickness absence	
	· Assessment of compliance with the standards of good clinical practice	
	· Questionnaire on global clinical impression; both, the doctor and the patient	
**Intervention**	There will be a weekly group session for 4 weeks (Only intervention Group)	
	Routine clinical practice	
**3-months post Intervention visit (V2)**	Variables:	
	· SF-12 Questionnaire	
	· Prescribed medicine	
	· Requested tests	
	· Derivations to secondary level	
	· Days of sickness absence	
	· Assessment of compliance with the standards of good clinical practice	
	· Questionnaire on global clinical impression; both, the doctor and the patient	
	· Assessment by the nurse subject participation.	
	· Assessment of cognitive- behavioral module by subject (Only intervention Group)	
**6-months post Intervention visit (V3) 12-months post Intervention visit (V4)**	Variables:	
	· SF-12 Questionnaire	
	· Prescribed medicine	
	· Requested tests	
	· Derivations to secondary level	
	· Days of sickness absence	
	· Assessment of compliance with the standards of good clinical practice	
	· Questionnaire on global clinical impression; both, the doctor and the patient	
	· Assessment of cognitive- behavioral module by subject (Only intervention Group)	

### **Variables**

#### ***Outcomes variables***

The main outcome variable is the improvement in 4 or more points in the area of Mental Healthcare from the SF-12 Quality of life at 12 months. The Spanish version of this Questionnaire has been validated: high inner consistency (range 0.77-0.92) for all the dimensions, except social function (0.55). The questionnaire is self-administered.

The secondary outcome variables recorded are:

– Questionnaire on Global Clinical Impression. Used to assess the patient's (PGI questionnaire) and the doctor’s (CGI Questionnaire) perceptions on the its improvement with the interventions. Will be administered at 6 months (to assess the effectiveness of the rules of good clinical practice) and at 12 months to evaluate the effectiveness of the intervention group added to the standards of good clinical practice. Will be treated as ordinal qualitative variable.

– Quality of life at 3 and 6 months after the intervention measured by the SF-12 questionnaire.

– Number of consultations during the period of study (broken down between nursing and medicine, each group session will be counted as a nursing consultation).

– Prescribed medicine during the period of study, with doubtful therapeutic value for their processing; related to the MUS. The included medicines are those related to the functional symptomatology:

– Pain: analgesic medicines, Nonsteroidal Anti-inflammatory Drugs and muscular pain reliever.

– Dizziness: vestibular sedatives, peripheral brain and vasodilators.

– Digestive Symptoms: pro-kinetics, anti-emetics.

– Asthenia: vitamin complex, restoratives, derived from ginseng, appetite stimulants.

– Anxiety: anxiolytics, antidepressants.

It will be regarded as quantitative variable, defined as the number of medicine taken during the period of study.

– Days of sickness absence during the period of study.

#### ***Clinical Variables***

– Duration of the somatic symptoms before the study. Quantitative variable (number of months).

– Time on anti-depressants consumption (months) before the study.

– Psychiatric Co-morbidity at the beginning of the study. It will be analyzed as a dichotomy qualitative variable (yes/no); assessing the presence/absence of depression, anxiety and somatic-morph disorders (according to the PRIME MD classification).

– PRIME-MD questionnaire; validated in Spain 
[27] that categorizes the patient into 5 areas of mental disorders with greater incidence on primary care: disorders in the state of mind/mood, anxiety disorders, disorders on nutritional behavior, somatoform disorders and disorders due to alcohol abuse or addiction. There are two components: a questionnaire for the patient that acts as a sifting/testing tool, and an assessment guide for the doctor that allows the diagnostic confirmation on the case. Once the questionnaire has been carried out, the patients diagnosed under anxiety or depression will be treated in a standardized way. Thus a bias is eliminated in the understanding of the study results, i.e. not to have treated the identified anxious-depressive psychiatric co-morbidity in a proper way; an issue that could have positive effect on the somatoform manifestations.

– Derivations carried out at secondary level.

– Complementary Tests, grouped in the following categories: laboratory, image tests, and endoscopies.

#### ***Sociodemographics descriptive variables***

Age, sex, cultural level, labor status on date of inclusion into the study.

#### ***Withdrawal***

Subject withdrawal criteria

a. The appearance of a pathological condition to explain the symptoms.

b. The use of an unusual alternative therapy (other than those normally used by the patient) for the treatment of symptoms, such as psychotherapy, etc. that could alter the outcome.

c. If the patient shows his/her desire to withdrawing from the study.

d. If the patient does not come to the follow-up visits.

If any of these events take place, it will be registered on the Case Report Form (CRF); stating clearly the date and the reason. The data will be equally processed to allow the analysis with intention to treat.

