### **Statistical Analysis**

The use of randomization by clusters conditions the statistical analysis that can be employed, especially in the calculation of confidence intervals and the testing of hypotheses. The following analyses will be undertaken:

1. **Descriptive analysis** of each variable with its corresponding CI at 95 %. Description of the profile of patients who abandoned the study plus their reason for withdrawal.

2. **Baseline comparison** of the two intervention groups in terms of the variables measured, prognostic factors and descriptive variables. Bivariate statistical tests will be used depending on the type of variable (qualitative or quantitative one).

3. **Analysis of primary outcome**: comparison of the proportion of patients that improve in 4 or more points in the area of Mental Healthcare from the SF-12 in both groups, at 12 months after patient inclusion, using the Chi-squared test, and the calculation of confidence intervals 95 %. Logistic regression with random effects will be used to adjust for prognostic factors; the dependent variable will be the improvement or not in 4 or more points obtained in Mental Healthcare; and the independent variable the intervention group to which each patient belonged. Confounding factors or factors that might alter the effect recorded will be taken into account in this analysis.

4. **Analysis of secondary outcomes variables**. The results of the secondary variables according to the assigned group will be compared for each secondary response variable using appropriate statistical tests.

All statistical tests will be performed with intention to treat. The last observation carried forward will be used for missing data. Significance was set at p < 0.05. All calculations will be made using SPSS© v.18 software.

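### Withdrawal for a new diagnosis, outside therapy or missed visits, with no stated SF-12 collection afterwards, lets a carried-forward score replace the 12-month outcome and weakens intention to treat

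*Protocol article*

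**What the plan says.** The Withdrawal section of the protocol article lists four criteria. Criterion (a) reads "The appearance of a pathological condition to explain the symptoms". Criterion (b) is use of a therapy the patient does not normally use, "such as psychotherapy, etc. that could alter the outcome". Criterion (c) is the patient's own wish to leave. Criterion (d) reads "If the patient does not come to the follow-up visits". The event is entered on the case report form with its date and reason, and the section closes: "The data will be equally processed to allow the analysis with intention to treat".

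Statistical Analysis repeats the principle, "All statistical tests will be performed with intention to treat", and adds one rule for gaps: "The last observation carried forward will be used for missing data". Its descriptive item treats withdrawn patients as having abandoned the study and plans to report their profile and reasons.

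The primary outcome, under Outcomes variables, is "the improvement in 4 or more points in the area of Mental Healthcare from the SF-12 Quality of life at 12 months". On blinding, the Masking section says: "In a study of this type it is impossible to mask the intervention".

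**The concern.** Criteria (a), (b) and (d) arise after centres have been allocated, and none is a refusal of further follow-up. Criterion (b) singles out patients because the event may affect the outcome, which is exactly where an intention-to-treat comparison needs the value actually observed at 12 months. If the SF-12 is no longer collected once a patient is withdrawn, that value is lost and an earlier score takes its place.

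The trial is unmasked and its intervention is psychological, so how often patients turn to other therapy could differ between arms. Unequal replacement of 12-month outcomes would distort the primary responder comparison. It would also add missing data that could be avoided, in a trial whose sample size allows for 10% loss at one year.

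**Working it through.** **The plan's own figures.** Sample size gives 50% against 30%, alpha 0.05, power 80%, 103 per arm, a design effect of 1.07 and 121 per arm after 10% loss.
- Two-sided, no continuity correction: n = [1.960·√(2·0.40·0.60) + 0.842·√(0.50·0.50 + 0.30·0.70)]² / 0.20² = 93 per arm.
- With continuity correction: (93/4)·[1 + √(1 + 4/(93·0.20))]² = 103 per arm, as stated.
- Design effect: 1 + (8 − 1)·0.01 = 1.07, and 103·1.07 = 110.21.
- Loss: 110.21·1.10 = 121.2, which matches 121. Dividing by 0.90 instead gives 122.5.

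The sample size reproduces, and this point does not change it.

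**What happens to a withdrawn patient under the text.**
1. Withdrawal section: the patient is withdrawn, and the data already held are kept for the analysis.
2. No section says that the 3-, 6- or 12-month SF-12 is still sought after withdrawal.
3. Statistical Analysis: a missing 12-month score is filled with the last one observed.
4. Taking the baseline visit (V1) as the reference, a patient withdrawn before the 3-month visit (V2) has a carried-forward change of 0. That is below 4 points, so the patient is a non-responder whatever happened later.
5. A patient withdrawn after V2 or V3 carries that visit's score, which may be a response or a non-response.

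**Illustration of size.** The article gives no withdrawal rates by arm, so every w and q below is an assumption. Let p be the true response proportion in an arm, w the fraction withdrawn, and q the proportion of the withdrawn who would have responded at 12 months. If all of them are carried forward as non-responders, the observed proportion is p − w·q.

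No true effect (p = 0.30 in both arms):

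| w intervention | w control | q | Observed | Spurious difference |
|---|---|---|---|---|
| 5% | 15% | 0.30 | 0.285 vs 0.255 | 3 points |
| 5% | 15% | 0.50 | 0.275 vs 0.225 | 5 points |
| 10% | 10% | 0.30 | 0.270 vs 0.270 | 0 |
| 10% | 10% | 0.50 | 0.250 vs 0.250 | 0 |

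Planned effect (0.50 vs 0.30, with q = p in each arm, so the observed proportion is p·(1 − w)):

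| w intervention | w control | Observed | Difference |
|---|---|---|---|
| 5% | 15% | 0.475 vs 0.255 | 22 points |
| 10% | 10% | 0.450 vs 0.270 | 18 points |
| 15% | 5% | 0.425 vs 0.285 | 14 points |

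Power for the 14-point case, with 121/1.07 = 113.1 effective patients per arm and no continuity correction: Φ{[0.14·√113.1 − 1.960·√(2·0.355·0.645)] / √(0.425·0.575 + 0.285·0.715)} = Φ(0.24) ≈ 0.60. The same formula at the planned 20 points gives 0.87.

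**The case against.** The strongest reply is that the article keeps withdrawn patients in the analysis. The closing sentence of the Withdrawal section and the general statement under Statistical Analysis both say so, and no text removes anyone from the analysis set or from the allocated arm. That stands. A reader might infer that the withdrawal criteria flatly contradict intention to treat; the documents do not support that. What is at risk is the observed outcome of these patients, not their place in the denominator.

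Second, the article never says that SF-12 collection stops. It condenses a full protocol that is not shown, and that document may provide for continued follow-up. This also stands, so the point is conditional on collection ending. It remains worth raising because what the article does state (withdrawal, patients who abandoned the study, a carry-forward rule) leads to substitution if followed as written.

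Third, a reader might infer that the bias favours the intervention, because controls know they receive no group sessions and may seek psychotherapy elsewhere. The documents do not establish this. The sessions in Table 3 give patients a psychological explanation of their symptoms and details of optional treatments, which could equally lead intervention patients to seek therapy. A figure built on withdrawals in the control arm alone, all frozen as non-responders, would be one-sided. Responses seen at 3 or 6 months could also be carried forward.

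Fourth, a patient who does not attend supplies no questionnaire whatever the label, and 10% loss is already allowed for. That holds for the missed visit itself. It does not justify letting a missed early visit count as withdrawal when the 12-month score might still be obtained.

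**Conclusion.** The point holds in a limited form. The article turns three kinds of post-allocation event into withdrawal, provides for no SF-12 collection afterwards, and fills the gap with an earlier score. That undermines intention to treat for the primary outcome, although the patients themselves are retained.

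The direction and size of any bias cannot be determined from the documents. The illustrative range runs from no spurious difference (equal rates, no true effect) to 3 to 5 points (5% vs 15%, no true effect). Under the planned effect, the observed difference is 14 to 22 points against a target of 20, depending on which arm loses more. These figures assume that outcome collection stops at withdrawal and that every withdrawn patient carries forward a non-response; they weaken to the extent that either assumption fails. The case for changing the text rests on how little it costs, not on a demonstrated bias.

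**What to change.** Amend the Withdrawal section so that:
- criteria (a) and (b) are recorded as events, with date and reason on the case report form, and do not end outcome collection;
- the SF-12 continues at V2, V3 and V4 for these patients, and the observed values are analysed in the arm to which their centre was allocated;
- non-attendance under (d) is treated as a missed visit, with V4 still sought;
- only withdrawal of consent ends follow-up.

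An analysis that censors at these events can be kept as a sensitivity analysis. If the full protocol already provides for this follow-up, a sentence saying so is enough.

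The change concerns data collection only and leaves clinical care as it is. The cost is protocol wording, a few more self-administered questionnaires from patients already enrolled, and some effort to stay in contact with them.
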